### 2.4. Recruitment

Women who fit the selection criteria will be invited to join the study. Subjects will then be selected using systematic random sampling. Informed written consent will be obtained at enrolment. Subjects will be briefed on the benefits and potential risks of joining the study.

Subject recruitment commenced in March 2021, and enrollment is expected to continue through October 2022. The research workflow is shown in Figure 1.

### 2.5. Measures

The outcomes of the study are mainly the anthropometric data, biochemical parameters, and energy as well as nutrient intakes. The primary variables of interest are dietary patterns and metabolomic profiles.

#### 2.5.1. Diagnosis of Type 2 Diabetes and Prediabetes

After an overnight fast of 8–12 h, subjects will undergo a 75 g, 2 h OGTT. Blood and urine samples will be taken for HbA1c, insulin, lipid profile, and metabolomic analysis. Subjects will be grouped into either NGT, prediabetes or T2D based on their OGTT and HbA1c results, as advised by the study endocrinologist. Our diagnostic criteria for T2D and prediabetes are based on the Malaysian Clinical Practice Guidelines [7] (Table 1).

#### 2.5.2. Sociodemographic Characteristics and Obstetric History

The study will collect sociodemographic data on age, ethnicity, education level, marital status, occupation, household income, and household size using a structured questionnaire. A family history of diabetes will also be assessed. Information on obstetric history will be obtained from the antenatal records. This will include gravidity, parity, pre-pregnancy weight, gestational weight gain, postpartum weight retention, number and timing of GDM diagnosis, duration lapse since GDM diagnosis, treatment during GDM, delivery method, birth outcomes, infant birth weight, breastfeeding duration, and family planning.

#### 2.5.3. Dietary Patterns

The study dietitian will administer a semiquantitative food frequency questionnaire (FFQ) adapted from the nationwide Malaysian Adult Nutrition Survey, to determine food consumption in the past month [21]. It contains 14 food groups: grain and cereal products; fast food; meat and poultry; fish and seafood; eggs; legumes, seeds and nuts; milk and dairy products; vegetables; fruits; beverages; alcoholic drinks; confectionaries; bread spread; and condiments. The portion size of the food items will be according to the Food Portion Sizes of Malaysian Foods Album [22]. The amount consumed food will then be converted into grams per day for each food item [10].

Dietary patterns will be derived based on PCA. Data suitability for factor analysis will be assessed prior to performing PCA [23,24]. Food items will be classified based on similarities in nutrient profiles and previous local studies [24,25,26]. The factor scores will be orthogonally rotated by varimax transformation to increase loading differences for easier interpretability [24,27]. Eigenvalue cut-off > 1.5 will determine the number of factors [28]. Food items with factor loadings < ±0.3 will be removed from further analysis [24,28]. A high factor score, whether positive or negative, indicates a high intake of that food group in dietary pattern; and vice versa [23,27].

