#### 2.5.4. Energy and Nutrient Intake

The study dietitian will administer 3-day 24 h dietary recalls. Subjects will be asked about the food and beverages consumed in the past 24 h. Other details will include the meal time, type of food and beverage, cooking method, and quantity or portion size. On the day of the visit, a 24 h dietary recall will be obtained. The research dietitian will later interview the subjects via phone calls to obtain another 2 days of 24 h dietary recalls. The 3 days of 24 h dietary recalls will be on nonconsecutive days (2 weekdays and 1 weekend).

Energy and nutrient intake calculations will be performed by the Nutritionist Pro software (V.5.1.0, Axxya Systems, Redmond, WA, USA). The serving size of the food and data on energy and nutrients will be obtained from the Nutrient Composition of Malaysian Foods database on the Nutritionist Pro software. If the food or beverage is not listed in the Malaysian food database, data will be obtained from the Singapore Food Composition database [29] and the U.S. Department of Agriculture database [30]. Recipes for local cuisine or mixed dishes will be created if they are unavailable on all databases. The average of 3-day dietary recalls will be obtained to determine the mean intake of energy and nutrients, including carbohydrates, protein, fat, fibre, vitamins, and minerals.

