### 2.7. Statistical Analysis

Statistical analysis will be performed using SPSS statistical software version 25.0 (IBM, Chicago, IL, USA). Data for categorical variables will be reported as number and percentage, while continuous data will be reported as mean ± standard deviation (SD). Data normality will be assessed prior to data analysis. The study will analyse the differences in the demographic characteristics between subjects who agreed to participate in the study versus those who did not agree to participate. Pearson’s correlation coefficient test will be used to determine correlations between continuous variables, the Chi-squared test to determine the association between categorical variables, and one-way analysis of variance (ANOVA) to compare the differences between the three groups. Multivariate linear regressions will determine the association between the metabolomic profile and factor scores of each dietary pattern yielded from PCA. Multinomial logistic regression will determine the factors, and the nutritype signature models associated with T2D. Variables significant at the bivariate level will be entered into the regression model as confounders. Crude and adjusted odds ratios (ORs) with a 95% confidence interval (CI) will be presented. Subgroup analyses will also be performed, such as early versus late postpartum (<1 year versus ≥1 year post-GDM), supplement versus nonsupplement users, and obese versus nonobese subjects. A previous study found different risk factors of T2D at early (<1 year) versus late postpartum (≥1 year) following GDM [4]. In case of missing data, the study will report the number of available data for the variable. We will analyse any differences in the characteristics between reporters versus nonreporters. A *p*-value < 0.05 for all statistical tests will be considered significant.

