Metabolomic profiles associated with dietary patterns have been previously studied in women post-GDM [14,15,16,17]. In the study by Andersson-Hall et al. involving 237 Scandinavian women post-GDM, linoleic acid was positively associated with vegetable oil and negatively associated with margarine intake. The linoleic acid level was reduced in women post-GDM who transitioned to T2D [14]. However, food intakes were calculated as the proportion of total diet (%) and not their absolute values in the study [14]. Another study involving 347 women post-GDM from the Nurses’ Health Study II found a correlation between dietary and plasma BCAAs [17]. Additionally, women post-GDM with higher dietary and plasma BCAAs had an elevated risk of T2D [17]. Serum and dietary polyunsaturated fatty acids were also correlated in the German study by Fugmann et al.; however, this study did not correlate dietary and serum fatty acids with the risk of T2D [15]. One study did not find any association between dietary glycaemic index and metabolites and did not assess the correlation between these parameters with the risk of T2D [16]. All of these studies [14,15,16,17] only focused on specific types of food or dietary components, instead of exploring dietary patterns as a whole. Only two studies [14,17] directly associated dietary intake and metabolites with the risk of T2D, indicating a paucity of evidence concerning nutritype signatures. Furthermore, all of these studies were conducted in the Western population, whose metabolomic profile may differ from that of the Asian population [49]. For instance, White European pregnant women had significantly lower glucose levels and most amino acid metabolites compared with South Asians, due to differences in body mass index and characteristics during pregnancy [49].

This study has a few limitations. The nature of the study is cross-sectional. Hence, the study will not be able to establish causation and effect. The study is limited to exploring only associations between dietary patterns, metabolomic profile, nutritype signatures, and T2D at a single time point. We also will not stratify subjects according to whether they have been practising certain treatments for T2D.

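### Pattern scores built from absolute g/day can carry part of the total amount eaten or reported, and the only stated covariate rule, a low-powered significance screen, may leave energy intake out of the models

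*Protocol article*

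**What the plan says.** Section 2.5.3 of the protocol article describes the input to the pattern analysis: "The amount consumed food will then be converted into grams per day for each food item". It continues: "Dietary patterns will be derived based on PCA". Varimax rotation follows, the number of factors is set by "Eigenvalue cut-off > 1.5 will determine the number of factors", and items with small loadings (cut-off 0.3) are removed. The section also provides for a check of data suitability and a regrouping of food items. It describes no scaling of intake to total energy.

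Section 2.5.4 measures energy with a different instrument: "The average of 3-day dietary recalls will be obtained to determine the mean intake of energy and nutrients". In Section 2.1 energy appears as a secondary outcome compared between the three glycaemic groups. It is not named as a covariate anywhere.

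Section 2.7 gives one covariate rule: "Variables significant at the bivariate level will be entered into the regression model as confounders". All tests use p < 0.05, and no covariate is named as always included.

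Section 2.5.9 codes the factor scores by sign and relates them to the NMR profile by PLS-DA. No covariates are mentioned there.

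**The concern.** Women who eat more, or report more, tend to record more grams of most foods. Absolute grams therefore share a quantity component, and scores derived from them can carry some of it. That component is linked to body size, physical activity and misreporting, and the Discussion itself lists under-reporting among the weaknesses of food-frequency questionnaires.

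Absolute grams are an acceptable input if energy is then handled in the models. Here that depends on a significance test. Such a test does not identify confounders, and at this sample size it will often miss a real difference in energy. An association of a pattern with type 2 diabetes, or with metabolites, could then mix diet composition with amount, although the study's question is about pattern. The issue also reaches the primary outcome, because the signatures are built from the same scores in a step with no stated adjustment.

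**Working it through.** **The plan's own figure.** No stated figure is in dispute. The sample size matters only through the power of the screen. If the 99 subjects of Section 2.3 are three groups of 33, then 33/0.8 = 41.25, rounded up to 42, and 3 × 42 = 126, as stated. Equal groups are an inference; the article gives no group sizes.

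**Step 1: chance that energy passes the screen.** Assume mean energy rises linearly over normal glucose tolerance, prediabetes and type 2 diabetes, by d SD from end to end. One-way ANOVA at 0.05 has noncentrality λ = Σ nᵢ(μᵢ − μ̄)². For equal groups of size n this is n·d²/2. With n = 42 and d = 0.5, λ = 42 × 0.25/2 = 5.25, and power on 2 and 123 degrees of freedom is 51%.

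| Group sizes (assumed) | d = 0.3 | d = 0.5 | d = 0.7 |
|---|---|---|---|
| 42/42/42 | 21% | 51% | 82% |
| 33/33/33 | 17% | 42% | 71% |
| 80/34/12 | 15% | 36% | 63% |
| 88/31/7 | 13% | 28% | 51% |

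A moderate energy difference is thus left out about half the time or more. This covers the screen against glycaemic group only, not the one for the metabolite regressions.

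**Step 2: how much quantity the scores carry.** This is a simulation with assumed inputs: n = 126; 14 or 30 food variables with log-normal intakes; three true patterns explaining 25% of item variance; a shared quantity component of 5–30%; PCA, eigenvalue above 1.5, varimax.

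| Mean absolute correlation of a rotated score with total intake | 14 variables | 30 variables |
|---|---|---|
| Absolute grams, no shared component | 0.55 | 0.48 |
| Absolute grams, shared component 5–30% | 0.59–0.65 | 0.52–0.58 |
| Intake as proportion of total, shared component 5–30% | 0.08 | 0.07 |
| Residual adjustment | 0 | 0 |

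The first row is mechanical: total intake is the sum of the same items. The shared component adds only 0.59 − 0.55 = 0.04 to 0.65 − 0.55 = 0.10 (14 variables), and 0.52 − 0.48 = 0.04 to 0.58 − 0.48 = 0.10 (30 variables). The zero in the last row holds by construction.

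**Step 3: consequence when the screen fails.** Same model, 30 variables, equal groups, 600 runs per setting. Only the amount eaten or reported differs by group (d = 0.5); composition does not. Recalled energy is assumed to share half its variance with that amount. Patterns were tested by ANOVA across groups, in place of the multinomial model.

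| Shared component | Energy passes | Any pattern significant, energy excluded | Same, nothing differs |
|---|---|---|---|
| 10% | 29% | 24% | 17% |
| 20% | 26% | 28% | 12% |
| 30% | 26% | 31% | 12% |

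The last column exceeds 5% because several patterns are tested. The excess due to quantity is therefore 24 − 17 = 7 to 31 − 12 = 19 percentage points.

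**Step 4: does the eigenvalue rule say anything about quantity?** With 14 variables sharing only a correlation r, the population first eigenvalue is 1 + 13r, which passes 1.5 at r = 0.5/13 = 0.038. But 14 completely uncorrelated variables at n = 126 give a first sample eigenvalue averaging 1.61, above 1.5 in 92% of runs; at n = 99 the figures are 1.69 and 99%. Passing the cut-off is not specific to a quantity component, so the conclusion does not use that threshold.

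**The case against.** - **Absolute intake looks deliberate.** The Discussion says of an earlier Scandinavian study: "However, food intakes were calculated as the proportion of total diet (%) and not their absolute values in the study". This stands, and it is why absolute grams should remain the main input. It does not require leaving energy out of the models.
- **The rule may not be exhaustive.** Section 2.7 says that significant variables are entered; it does not say that nothing else is, and it does not name energy. A fuller plan could add covariates. This stands as a limit: applying the rule to energy is an inference. The point is nevertheless about a stated rule, and the article gives no other route.
- **Energy is one case of a general weakness.** Selection by significance affects age, BMI and time since GDM equally. True, but energy is tied directly to the unit in which the patterns are built.
- **Adjustment can change the question.** If amount eaten lies on the path from diet to diabetes, conditioning on energy alters what is estimated. This is fair, and a reason to report both results.
- **A reader might infer that a pattern would simply measure how much a woman eats, or that a pure quantity factor is bound to be retained.** The documents do not support either. Varimax spreads any quantity component over several patterns, items are regrouped before the analysis so the number of inputs is unknown, and noise alone passes the 1.5 cut-off.

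**Conclusion.** The point holds in a moderate form. The article derives patterns from absolute grams per day and states only a significance screen for covariates. Pattern scores can therefore carry part of the total amount eaten or reported, and energy may be left out although it is collected. For a 0.5 SD end-to-end difference, the chance of being left out is about 49% with three groups of 42 and 64–72% under the two unequal splits shown. In the simulated case where only amount differs, false pattern findings rise by 7 to 19 percentage points when energy is excluded.

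These sizes rest on assumed group sizes, effect sizes, variance shares and reliability of recalled energy, none of which the documents give. The text itself supports the direction of the problem, not its exact size. Nothing in the article is miscalculated or contradictory on this point. It is a cheap improvement.

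**What to change.** 1. Keep absolute grams per day for the main PCA.
2. In Section 2.7, enter total energy intake in every linear and multinomial model that contains factor scores, regardless of its bivariate p-value, and report results with and without it.
3. Add one sensitivity PCA on energy-adjusted (residual) food-group intakes, and carry it through the sign coding, PLS-DA and signature models of Section 2.5.9. Without this, the primary outcome stays untouched, since a regression covariate does not reach the PLS-DA step.

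**Cost.** Plan wording and analysis time; no new data. Energy adds one parameter per contrast to the multinomial model, which matters if there are few women with type 2 diabetes. The prevalence range in the Discussion, 0.8% to 35.5%, would mean about 1 to 45 of 126 (0.008 × 126 = 1.0; 0.355 × 126 = 44.7). Correction will be partial: energy comes from three 24 h recalls and the patterns from a questionnaire on the past month, so misreporting on the questionnaire is only partly captured.

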### 2.3. Study Population

The study will include Malaysian women aged 18–49 years with a previous diagnosis of GDM. Exclusion criteria will be the following: pregnant women, recent hospitalisation within the last 6 weeks, and previously diagnosed medical problems (such as type 1 or type 2 diabetes, cancer, and liver or renal disorders). The sample size will be estimated using the mean difference formula [20]. Based on a study that compared dietary intake and metabolomic profile in NGT, prediabetes and metabolomic profile in women post-GDM in Gothenburg, Sweden [14], considering a 95% confidence level and 80% power, a total of 99 subjects will be needed for the study. To account for nonresponse or refusal to participate, an additional 20% of subjects will be required, leading to a minimum of 126 subjects.

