#### 2.5.9. Nutritype Signatures

Nutritype signature models will be developed based on the three-step chemometric strategy for nutrimetabonomics [42,43]. In step 1, dietary patterns, as assessed by PCA, will be used to identify the factor scores as described in Section 2.5.3. The factor scores will then be designated as “loadings (VFFQ)”. In step 2, factor scores will be coded to create dummy variables (UFFQ). Positive scores will be coded as class number one, whereas negative scores will be coded as class number two. In step 3, the coded factor scores of each dietary pattern will be regressed against the ^1^H NMR metabolite profile to identify the metabolic phenotypes (“loadings, VNMR”) associated with these dietary patterns using PLS-DA to maximise the separation between T2D and non-T2D groups. The corresponding loading plots from the PLS-DA analyses will determine the significant metabolites we will use to develop nutritype signature models [25]. Chemometric analysis will be performed to produce nutritype signature models using SIMCA-P 15.0+ software (Sartorius Stedim, Umeå, Sweden).

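### Section 2.5.3 reads a large factor score of either sign as high intake, which is wrong for signed PCA scores and conflicts with the sign-based classes in Section 2.5.9

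*Protocol article*

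**What the plan says.** Section 2.5.3 of the protocol article fixes the method: "Dietary patterns will be derived based on PCA". On rotation it says "The factor scores will be orthogonally rotated by varimax transformation to increase loading differences for easier interpretability", and on retention of foods "Food items with factor loadings < ±0.3 will be removed from further analysis". It then closes with the rule for reading the result: "A high factor score, whether positive or negative, indicates a high intake of that food group in dietary pattern; and vice versa".

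Section 2.5.9 takes these scores into the nutritype models. In step 1, "The factor scores will then be designated as" is followed by the name loadings, with the symbol VFFQ. In step 2, "Positive scores will be coded as class number one, whereas negative scores will be coded as class number two". In step 3 the two classes are related to the NMR profile by PLS-DA.

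Section 2.7 also uses the scores as continuous variables: "Multivariate linear regressions will determine the association between the metabolomic profile and factor scores of each dietary pattern yielded from PCA". Neither Section 2.5.9 nor Section 2.7 says which class, or which end of the score, stands for closer adherence to the pattern.

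**The concern.** A factor score belongs to a woman and has a direction. Two women with scores of equal size and opposite sign lie at opposite ends of the pattern. The rule in Section 2.5.3 gives both the same description, high intake.

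Section 2.1 makes the nutritype signatures associated with T2D the primary outcome. These signatures are built from the sign-coded scores, and the result is a statement about direction: which diet goes with which metabolites, and which of these go with T2D. The rule in Section 2.5.3 is the only guidance a reader has on what a negative score means. Applied as written, it would attach the wrong diet to a correctly computed association, in a study whose findings are meant to support prevention measures (Section 3).

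**Working it through.** The documents give no figure on this point, so there is none to reproduce. The check is algebraic, with a simulation for scale.

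**1. What a signed score implies.** Assume PCA on standardised intakes with scores scaled to unit variance. This is not stated, but it fits an eigenvalue cut-off of 1.5. Write z for the standardised intake of a food, λ for its rotated loading and s for a woman's score. Scores have mean zero, varimax keeps them so, and the correlation between z and s equals λ. The least-squares fitted intake at score s is therefore

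fitted z = λ × s.

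Take loadings at the retention limit of 0.3 in Section 2.5.3, and scores of +1 and -1 for illustration:

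| Loading λ | Score s | Fitted intake λ × s | Section 2.5.3 rule |
|---|---|---|---|
| +0.3 | +1 | +0.3 SD (above average) | high |
| +0.3 | -1 | -0.3 SD (below average) | high |
| -0.3 | +1 | -0.3 SD (below average) | high |
| -0.3 | -1 | +0.3 SD (above average) | high |

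The rule is right only where score and loading have the same sign. Row 2 shows the error when the rule is read for scores. Row 3 shows it when the rule is read for loadings.

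**2. Consistency with Section 2.5.9.** If the rule were true, strongly positive and strongly negative scorers would both be high consumers. A split into class one (positive) and class two (negative) would then not separate diets. The split makes sense only if the two signs mean opposite things, as the algebra says. The two sections cannot both be right, and Section 2.5.9 has the usable reading.

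**3. Use of the scores.** Section 2.5.9 codes them by sign and Section 2.7 regresses on them as they stand. Nothing in the article takes an absolute value. Deleting the rule would change no class assignment, coefficient or odds ratio.

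**4. Scale.** The simulation used 14 food groups (Section 2.5.3), 126 women (Section 2.3), an eigenvalue cut-off of 1.5 and varimax, with 500 runs for each of two intake distributions. Assumptions not in the documents are the three-pattern loading structure, the shape of the intakes, the cuts at -1 and +1, and that each component is oriented so that its main foods load positively. Intake is the mean standardised intake of foods loading above +0.3.

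| Quantity | Normal intakes | Right-skewed intakes |
|---|---|---|
| Share of women with score below -1 | 15.9% | 10.7% |
| Their mean intake of the pattern's foods | -1.18 SD | -0.83 SD |
| Share of women with score above +1 | 15.9% | 13.7% |
| Their mean intake of the pattern's foods | +1.18 SD | +1.46 SD |
| Correlation of signed score with intake | 0.99 | 0.99 |

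Women whom the rule would call high consumers because of a strongly negative score thus eat about 0.8 to 1.2 SD less than average of the foods that define the pattern.

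**The case against.** The strongest reply is that no analysis uses the sentence. The coding and the regressions work on signed scores, so the numbers come out the same whatever the sentence says. This stands, and it limits the point to the wording of results.

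A second reply is that the sentence is a slip for loadings. The sentence before it is about loadings, and it speaks of a food group, which has a loading and not a score. A large loading of either sign does mark a food that matters to the pattern. This is plausible, and on that reading no woman is misdescribed directly. But a large negative loading marks a food eaten less by high scorers, so high intake is still the wrong description.

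A third reply concerns the label VFFQ in step 1 of Section 2.5.9. It follows a cited chemometric strategy that is not at hand, so whether the label departs from that source cannot be checked. This also stands. The request there is only for consistent terms within the article.

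A reader might infer more than the text supports:

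- That the diet of about half the women is reversed, because about half of the scores fall below zero. The sentence speaks only of high scores and sets no cut-off, so a woman just below zero is not called a high consumer.
- That a real association would vanish, because the absolute score carries no linear information. No model uses the absolute score, and the argument needs a symmetric score. With right-skewed intakes in the simulation, the absolute score still correlated about 0.55 with intake.
- That the 0.3 cut ignores negative loadings. The plus-minus sign already makes it a cut on absolute size.

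**Conclusion.** The point holds as an error of interpretation. The rule in Section 2.5.3 is false for factor scores, false for loadings if those were meant, and inconsistent with the opposed classes in Section 2.5.9. It is an explicit wrong statement, not detail left to a fuller document.

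No planned estimate or class assignment changes. What is at risk is the description of strongly negative scorers, and hence of class two in the models behind the primary outcome, and so the stated direction of the diet, metabolite and T2D associations. The documents give no share of women affected. The 11% to 16% per pattern is illustrative and depends on the assumed loading structure and the cut at -1. The algebraic conclusion does not depend on these choices.

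**What to change.** 1. In Section 2.5.3, replace the closing sentence with: *A higher (more positive) factor score indicates greater adherence to the pattern; a negative score indicates below-average adherence, that is, lower intake of positively loading foods and relatively higher intake of negatively loading foods.*
2. Report the sign of each retained loading with its size, so that the direction of every pattern can be read from the table.
3. In step 2 of Section 2.5.9, state that class one is above-average and class two below-average adherence.
4. Use the word scores for values that belong to women and loadings for values that belong to food groups, including in step 1 of Section 2.5.9.

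The cost is a few sentences. No new data, re-analysis or change to the sample size is needed, and the 0.3 retention rule can stay as it is.
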